### Setting

The setting for this study is a Mental Health Crisis Intervention & Brief Therapy team (CI&BT team) in a large city, where patients with severe psychiatric and psychosocial problems come into contact with the CI&BT team during crisis. Therapists in this team are treating these patients on an outpatient basis for a period of a maximum of six months after the crisis.

Clients of different ages – with a minimum of 18 years – are referred by GPs, self-employed therapists, mental health outpatient clinics and the police. Treatment is given at the centre of the CI&BT team. There is no diagnostic screening beforehand: the CI&BT team starts immediately on a combination of diagnosis and treatment.

#### Participants

This is a mixed diagnostic group of patients with acute psychiatric problems: axis I conditions, problems resulting from personality disorders (axis 2 problems such as borderline or anti-social personality disorders) and serious psychosocial problems (severe family conflicts, anti-social behaviour).

The distribution of principal diagnoses in the past years (2009–2011) was as follows: 21% with a psychotic disorder, 16% with an adaptive disorder, 10% with a depressive disorder, 9% with an anxiety disorder, 8% with a disorder associated with substance abuse and 5% with a bipolar disorder, 6% with the principal diagnosis of personality disorder, 3% without a score or deferred, 1% cognitive/organic disorder, other 31%.

After ending treatment 30% of the clients entering the CI&BT team was referred to other clinics.

### Measurement instruments

#### PCOMS

PCOMS contains two very short questionnaires consisting of four items each, one for determining the outcome and the other for determining the quality of the working alliance. The patient is required to complete these questionnaires at every session. So outcome and alliance can be discussed immediately by therapist and client on a session-by-session basis. Duncan and Miller [44] developed PCOMS, two short questionnaires for obtaining feedback as simply and effectively as possible about both the alliance and the effect of the treatment. They describe the use of these two questionnaires as 'Client Directed Outcome Informed' (CDOI) practice. PCOMS is a methodical tool: therapists continue to work according to their own therapy model. Characteristically, PCOMS visually describes satisfaction with the therapeutic relationship (i.e. the alliance) and development of client well-being (i.e. the outcome), using simple scoring lists. For this purpose the ‘Outcome Rating Scale’ (ORS) and the ‘Sessions Rating Scale’ (SRS) are used. The questionnaires are completed and discussed at every session. In the slightly longer term, the ORS is an indicator of perceived effect of the treatment as a whole and, in combination with the SRS, provides a timely indication of any stagnation in the therapy. When a client has doubts about the alliance, these emerge as a low score on the SRS. A persistently poor alliance is associated with a high drop-out risk [14].

#### Outcome rating scale

The ‘Outcome Rating Scale’ (ORS), the ‘How are you?’ form, measures client assessments of various areas of their functioning. The ORS is discussed briefly at the beginning of every session. When change is evident compared to the previous session(s), the discussion fixes its eye upon the significance of that change. This discussion can be minimal or extensive depending on the information obtained. The form consists of one A4 form with four visual analogue scales all relating to an aspect of client well-being: ‘individual’, ‘relational’, ‘social’ and ‘general’. The clients are asked to place a cross or hash mark somewhere on each line as an assessment of their functioning in the period prior to the session. The far left of the line is ‘poor’; the far right is ‘good’. On a line measuring 10 cm, this results in a score between 0 and 10. Internal consistency for the English version of the ORS is .93 and validity has been demonstrated by studying the correlation with the OQ-45 [17].

#### Session rating scale

The ‘Session Rating Scale’ (SRS), the ‘What did you think of the session?’ form, measures various aspects of the alliance and it is completed at the end of the session. This also is a single form with four lines, being scored in the same way as the ORS form. It looks at four aspects of the treatment session: the relationship, the goals, the approach and the session as a whole. The questionnaires are completed and discussed at the end of every session. When the crosses on the ‘What did you think of the session?' form indicate reticence or plain dissatisfaction, questions are asked about the subject of dissatisfaction. Relatively limited criticisms can be discussed immediately. In case of structural comments or criticisms an appointment is made to discuss these at length during the following session. A check is made to see whether there is enough confidence on the client's side to ensure that the client will return for the next session.

Internal consistency of .88 has been found for the English version of the SRS, and a correlation of .48 has been found with the HAQ-II [26].

The English version of the CDOI questionnaires has now been adequately validated [50,51]. The indications for the Dutch version are that the questionnaires are psychometrically reliable [52,53]. The translation of the ORS and SRS was made by Hafkenscheid et al. [39]. Details of this translation were adapted in consultation with a number of Dutch therapists, and Duncan and Miller; a translation of the principles of the CDOI method is made by [name] [54].

#### Choice of feedback instrument in this study

PCOMS elaborates on existing instruments such as the OQ 45, but offers a much shorter score list. Miller et al. [27] have argued that time-consuming procedures interfere with the implementation of feedback, therefore a short measure has an important advantage in the light of the necessity of applying session-by-session feedback.

Since there is little time and attention for scoring questionnaires in emergency psychiatry, score lists have to be short, but at the same time provide a broad spectrum of information about complaints as wel as about general wellbeing. Information about the therapeutic alliance should be gathered in an equally efficient way. Since therapy outcome and satisfaction with the alliance are measures in PCOMS using straight forward scoring lists which can be completed quickly, the ‘Outcome Rating Scale’ (ORS) and the ‘Sessions Rating Scale’ (SRS) are the preferred instrument for this setting.

This need for an easy-view instrument also applies to the therapists who have, during the crisis phase, little time and attention left for elaborate explanation and filling out forms. Also, the CI&BT team handles psychiatric as well as psychosocial problems, so therapists will prefer a feedback instrument that can refer to both aspects of a crisis situation.

### Interpretation and consequences of the ORS and SRS scores

#### ORS

When change occurs compared with the previous session, the therapist is instructed to discuss the significance of that change. Is it related to the treatment or is a life event influencing the well-being at this point? Therapists will be informed about expected treatment curves (ETC) based on empirically derived decision rules [21] and instructed to compare actual progress to the ETC. During the initial sessions (mild) improvement should be visible, the absence of any improvement is considered to be an important predictor of therapy failure and drop-out.

#### SRS

A low score on the SRS form may indicate client doubts about the alliance. This need not be a problem when the ORS form indicates that well-being is improving. Therapists are instructed to detect potential breaches in the alliance. Breaches are defined as a score less than 36 in total or less than 9 on any item of the SRS. It is made clear to the client that the SRS score intends to facilitate a conversation about the alliance between client and therapist and that no one has to be offended by the SRS scores since they offer a way for therapists to improve and tailor services based on client preferences.

When a low ORS score fails to rise after a few sessions, the case should be discussed in intervision/supervision or a colleague should be consulted. If better scores still fail to materialise after about seven sessions, referral to another therapist is the appropriate option.

Although therapists will be strongly encouraged to openly discuss the feedback with clients, the frequency or content of these interactions is not formally monitored.

Adherence to the feedback system will be stimulated by regular supervision sessions.

### Outcome questionnaire 45

The Outcome Questionnaire 45 (OQ-45) is a self-report questionnaire developed by Lambert [55] with the aim of mapping out the course of client symptoms during and after the end of the treatment by means of the structural completion of the questionnaire. The list consists of 45 statements leading to three subscales that are aimed at assessing different domains of client functioning: Symptom Distress, Interpersonal Relations and Social Role. Scores are generated for each subscale and the total score is obtained by summing up the three subscores. The internal consistency for the Total score of the Dutch OQ-45 ranges between 0.92 and 0.96 in university, community, patients and community and patients combined samples. For the subscales the consistency is 0.90- 0.95 for the Symptom Distress scale, 0.74-0.84 for the Interpersonal Relations subscale and 0.53-0.72 for the Social Role subscale [56].

### The brief symptom inventory (BSI)

The Brief Symptom Inventory [57] is the concise version of the Symptom Checklist 90 and consists of 53 statements. The BSI is a self-report questionnaire for measuring symptoms of psychopathology in adults. The patient is asked to state on a five-point scale ranging from ‘very much so’ to ‘not at all’ the extent to which the statement has been applicable to him/her during the previous week. The results lead to a general score and three sub-scales: the Global Severity Index (GSI), Positive Symptom Distress Index (PSDI), and Positive Symptom Total (PST). The questionnaire was translated from English to Dutch and then back-translated before the original version was compared with the translation. In addition, the Dutch translation was compared with the translation of the Symptom Checklist-90 and the definitive translation was then adopted after a number of changes had been made [57]. Reliability (i.e. the alpha coefficient) of seven of the eight scales was > .80 and this means that reliability is satisfactory. The only exception is the psychoticism scale (.71). The reliability of the scale as a whole is .96. Validity was examined by linking the BSI to the Symptom Checklist-90-R and a few other scales for psychopathology.

### Helping alliance questionnaire

The Helping Alliance Questionnaire (HAQ-II) is a questionnaire developed by Luborsky [58] that maps out the alliance between the patient and the therapist as perceived by the two. Both state independently, in response to 19 statements, the extent to which they agree with the description of the alliance on a six-point scale ranging from 'disagree entirely' to 'agree entirely'. Luborsky et al. report internal consistency reliabilities (alphas) of 0.90 to 0.93 and test-retest reliabilities of 0.56 to 0.78; a further study reported alphas of 0.85-0.91 [58].

The questionnaire was translated from English to Dutch and then translated blindly back to English. The Dutch version of the HAQ-II has been psychometrically evaluated [59].

### Clinical global impression

The Clinical Global Impression (CGI) [60] is a very short instrument consisting of two questions to be completed by the therapist. The CGI is mostly used for making a global assessment. The first question relates to the global severity of the patient's problems, as established on a seven-point scale ranging from ‘normal/not a problem’ to ‘very severe problem’. The second question relates to global change as compared to the status at the outset of the treatment, which can also be stated on a seven-point scale ranging from ‘major improvement’ to ‘major decline’. The CGI has been widely used in clinical research concerning social anxiety [61] and depression [62] and (most often) one and the same format of the CGI is being used for studying various sorts of pathology. The question of the validity of the CGI is still debated [61].

### Satisfaction questionnaire

This first author devised this questionnaire with the aim of establishing patient satisfaction after the termination of the treatment. The questionnaire comprises two separate components: the first is completed by all patients and consists of a five-point scale that allows patients to state the extent to which they are satisfied with different aspects of the treatment. The second component is restricted to patients in the experimental condition. It allows patients to state on a five-point scale to what extent they are satisfied about the use of PCOMS. As the questionnaire was developed especially for this research the reliability and validity haven’t been established yet.

### Attitude questionnaire

This is a questionnaire developed by Morton Anker in 2005 [31] that asks the therapists about their attitude to the PCOMS instrument (both the ORS and SRS). This is done using 19 statements and therapists are required to state the extent to which they expect the instrument to make a – positive or negative – contribution to the treatment outcome on a five-point scale ranging from ‘entirely agree’ to ‘entirely disagree’. The reliability nor the validity of this questionnaire have been researched yet.

### Ethical approval and consent

The study protocol and informed consent procedure was evaluated in 2009 by the ethics committee for Dutch Mental Health Institutions, (Kamer Noord of the METiGG) (approval nr. 9219, 1-9-2009).

The Committee concluded it to be an extremely useful and clinical relevant research project, that does not fall under the jurisdiction of the WMO (the Dutch law on scientific medical research on human beings) as the use of the applied questionnaires are common practice in mental health care. Furthermore that discussing how patients are getting on and how they experience the alliance does not add any additional burden or risk for the patient, since this in fact is a basic ingredient of every psychotherapy. As a consequence the regular clinical procedure for informed consent at the department was followed. The study was explained to the patients, written information was provided and patients were asked to participate on a voluntary basis, which was noted in the medical file.

### Data analysis

#### Sample size calculation

With two groups of 90 patients, an alpha of 0.05 (one-tailed), an effect size of about 0.3 on the Global Severity Index at 12 weeks (mean EXP group = 1.0; mean TAU = 1.3; standard deviation at week 12 is 0.80) can be detected with a statistical power of 80%. Analysis will be performed according to the intention to treat principle.

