**Method/Design:**

To test the hypotheses, all patients seeking help from the Crisis Intervention & Brief Therapy Team over a two-year period will be followed throughout their treatment up to a maximum of six months and a follow-up period of three months after ending the treatment. Patients are randomly assigned to two conditions: treatment without feedback and treatment with immediate feedback for each session. The therapists all operate in both conditions and so they deliver both treatments. An estimated total of 180 patients, aged 18 years and over, will be included in the study.

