#### Primary analysis: EXP versus TAU

In the primary analysis, outcomes of the two treatment conditions will be compared using repeated measures analysis (GLM), with the number of sessions as a covariate. In this analysis, each follow-up measurement will be compared separately to the baseline measurement. Since in this design patients are nested within therapists, these nested data will also be examined in a multilevel analysis, controlling for therapist variation. The number of sessions will be included as a covariate.

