## Conclusion

All these factors make it awkward to interpret findings in a consistent manner. For example, it is difficult to determine to what extent the method adopted, the number of sessions, the time elapsed or other factors such as feedback determine the treatment outcomes. It is also the question whether clients who find themselves in a crisis, often precisely because of a lack of ability to think about their own situation or to cooperate with the mental health services, can benefit from more feedback and reflection, and whether this does not actually impose an additional burden on the relationship. It is also difficult to determine the extent to which the quality of the alliance is affected by changes in the therapist and/or working in co-therapy, and whether this might have offset any possibly positive effect of feedback. The participation of a relatively large group of less experienced staff may also affect the quality of the feedback process in the sense that inexperienced staff may become unsure in crisis situations when faced by critical feedback so that the feedback has less effect or is even counter-productive. Finally, the basic treatment in the EXP and TAU groups will be delivered using the specific treatment model developed in the CI&BT team, which had traditionally put a strong emphasis on motivating, client-driven approach (e.g. approaching care avoiders), with the desires and objectives of the client and people closely concerned occupying a central position. The drawback here is that adding formal feedback through CDOI may generate less added value than in a traditional treatment setting.

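### The trial is sized on a one-tailed 5% test with no reason given, although the paper leaves open whether feedback helps or burdens patients in crisis; at a two-sided 5% level the power is about 71%, not 80%

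*Protocol article*

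**What the plan says.** The Sample size calculation states "With two groups of 90 patients, an alpha of 0.05 (one-tailed". It assumes "mean EXP group = 1.0; mean TAU = 1.3" on the GSI and says that the "standard deviation at week 12 is 0.80". From these it claims 80% power. The Abstract gives the same total: "An estimated total of 180 patients, aged 18 years and over, will be included in the study". No reason for the one-tailed choice appears in this section or elsewhere in the article.

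Under Primary analysis: EXP versus TAU, outcomes "will be compared using repeated measures analysis (GLM", with number of sessions as a covariate. Each follow-up is compared separately with baseline. The section does not say whether the test is one-sided or two-sided.

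The research questions at the end of the Background are worded in the direction of benefit. The Conclusion is less certain. It asks whether clients in crisis can benefit from more feedback and "whether this does not actually impose an additional burden on the relationship". It adds that inexperienced staff may become unsure when criticised, so that "the feedback has less effect or is even counter-productive".

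**The concern.** A one-tailed test suits a trial in which an effect in the other direction is impossible, or would lead to the same action as no effect. The article claims neither. Its Conclusion treats a burden on patients as an open question, and the Background says it is unsettled whether feedback instruments should be introduced in daily psychiatric practice. A worse outcome with feedback would bear directly on that decision.

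Two things are at stake. First, the chance of falsely declaring benefit is 5%, twice what a two-sided 5% test allows in that direction. Second, the declared rule has no outcome called harm: however large a deterioration in the feedback arm, it is reported only as a failure to show benefit. Because the analysis section is silent on sidedness, a reader also cannot tell which error rate will apply to the reported result.

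**Working it through.** **Inputs, all from the Sample size calculation.** n = 90 per arm; GSI means 1.0 and 1.3, so a difference of 0.3; SD 0.80; alpha 0.05, one-tailed; stated power 80%. The standardised difference is 0.3 / 0.80 = 0.375. The figure of about 0.3 that the section calls an effect size is the raw difference.

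**Step 1: reproduce the stated power.** Two-sample t-test with df = 2 × 90 − 2 = 178 and noncentrality 0.375 × √(90/2) = 2.516.
- One-sided critical value 1.653: power 80.5% (normal approximation 80.8%). 80% needs 89 per arm.

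The stated 80% with 90 per arm therefore reproduces on its own inputs.

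**Step 2: the same inputs, two-sided 5%.**
- Critical value 1.973: power 70.6% (normal approximation 71.1%).
- 80% needs 113 per arm, 226 in total, against 180 planned. The normal approximation gives 112 per arm.
- The chance of missing the assumed effect rises from about 20% to about 29%.

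**Step 3: what this means on the GSI scale.** The standard error of the difference is 0.80 × √(2/90) = 0.119. The smallest observed benefit declared significant is 1.653 × 0.119 = 0.197 under the one-tailed rule and 1.973 × 0.119 = 0.235 under the two-sided rule. A result between these values is a claimed benefit under one rule and not under the other.

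**Step 4: what baseline GSI can recover.** The article gives no correlation ρ between baseline and week-12 GSI, so ρ is an assumption here. With baseline as a covariate, the effective standardised difference is 0.375 / √(1 − ρ²). For change from baseline with equal SDs at both times (also assumed), it is 0.375 / √(2(1 − ρ)). Two-sided power with 90 per arm:

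| Assumed ρ | Baseline as covariate | Change from baseline |
|---|---|---|
| 0.4 | 0.409 → 78% | 0.342 → 63% |
| 0.5 | 0.433 → 82% | 0.375 → 71% |
| 0.6 | 0.469 → 88% | 0.419 → 80% |

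With the covariate, power reaches 80% at ρ of about 0.45. No figure here allows for dropout or for patients sharing therapists.

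**The case against.** The strongest reply is that nothing is hidden or miscalculated. The article openly declares one tail, its 80% is right for that test, the research question is directional, and the Abstract says earlier data point strongly to benefit. The full protocol may give a reason that the article omits. The ethics committee, as reported under Ethical approval and consent, saw no added burden or risk in discussing progress and alliance.

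Much of this stands. The 80% is not an error, and a reader can convert it. A directional hope, however, does not exclude an effect the other way, and the authors themselves still raise burden as a question in their Conclusion.

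Three stronger readings are tempting, and the article does not support them:
- A reader might infer that the trial sets out to ask whether feedback is counter-productive. That remark is one limitation, conditional on inexperienced staff, and is not a research question. The burden question is general, but it concerns the therapeutic relationship and not the GSI.
- A reader might take the two earlier feedback studies in patients with psychiatric disorders, which found no overall effect, as evidence of harm. They were null overall; the second reported prevention of negative change in not-on-track cases in short-term therapies, and the Background describes its population as only mildly distressed.
- A reader might infer that a repeated-measures GLM can only give a two-sided test, so that sizing and analysis contradict each other. With two arms, each comparison of a follow-up with baseline is a single-degree-of-freedom contrast, which can be tested one-sided. The defect is that the sidedness is not stated.

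The 71% also has a limit: it is an unadjusted week-12 comparison. It equals the power of the change-from-baseline comparison only if the correlation is 0.5 and the SDs are equal.

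**Conclusion.** The point holds as an unjustified design choice, not as an arithmetic error. The one-tailed 5% alpha doubles the allowed false-positive rate for benefit relative to a two-sided 5% test and leaves no way to declare harm, in a paper that treats the direction of effect in these patients as unsettled. On the stated difference, SD and group size, two-sided power is about 71% unadjusted, roughly 10 percentage points below the stated figure. The covariate figures of 78% to 88% rest on assumed correlations and on a term that the primary analysis section does not name. The change should be made, but it does not undermine the rest of the design.

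**What to change.** In both the Sample size calculation and the Primary analysis section, state that the primary week-12 GSI comparison is two-sided at 5%, reported with a 95% confidence interval. Restate power for 90 per arm, a difference of 0.3 and SD 0.80 as about 71% unadjusted.

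In the primary analysis, enter baseline GSI as a covariate in place of the comparison of change from baseline. Give the assumed correlation with its source and the resulting power, and say whether dropout and therapist clustering are allowed for.

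The cost is a less favourable stated power and a change to the primary model, which goes beyond wording but uses a baseline measurement already planned. If the correlation is about 0.5 or higher, no extra patients are needed to reach 80% before dropout and clustering. If it is lower, the sponsor must either accept power somewhat under 80% or recruit more; without any adjustment, two-sided 80% would take 226 patients instead of 180.

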### Feedback instruments

The feedback studies that meet the requirements that can be derived from the findings of Knaup as mentioned above, are the studies using the Outcome Questionnaire 45 (OQ45) of Lambert and the Partners for Change Outcome Management System (PCOMS) of Miller and Duncan [26,27]).

In the most recent meta-analysis, Lambert & Shimokawa [28] performed a meta-analysis of the effects of both the OQ45 and PCOMS, including a total of 9 randomized controlled trials. This study comprises six randomized studies on the OQ45 and three randomized studies on PCOMS. The latter concerning individual therapy in a student counselling university setting [29], and couples therapy in the context of an (American) university therapy training programme [30], respectively a (Norwegian) family counselling agency [31].

Lambert & Shimokawa found effects sizes varying from .23 to .33. They concluded that the number of psychotherapy patients who deteriorate (5–10% in adult therapy, 14–24% in child psychotherapy, in routine care) can be cut in half by use of these systems. Here also, the main effect comes from identifying Not On Track clients in good time. However, in some of the studies analyzed also beneficial effects were reported for ‘On Track’ clients [31-33].

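### The sample-size statement calls a raw difference of 0.3 GSI points an effect size of 0.3; the standardised effect that has 80% power is 0.375

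*Protocol article*

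**What the plan says.** The protocol article, under Sample size calculation, starts from "With two groups of 90 patients" and "an alpha of 0.05 (one-tailed"). It says that the trial can then detect "an effect size of about 0.3 on the Global Severity Index at 12 weeks (mean EXP group = 1.0; mean TAU = 1.3". The same parenthesis goes on to give the SD, and the sentence ends with the power: "standard deviation at week 12 is 0.80) can be detected with a statistical power of 80" per cent.

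The Background uses the same term for results of earlier feedback research. Under Results of feedback, two meta-analyses are cited with average effect sizes of 0.39 and 0.10. Under Feedback instruments, a meta-analysis of nine randomised trials of the OQ45 and PCOMS systems is reported with "effects sizes varying from .23 to .33".

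**The concern.** The number 0.3 equals 1.3 minus 1.0, a difference in GSI points. It is presented as an effect size although the SD next to it is 0.80 and not 1. Rounding does not explain it, since 0.375 to one decimal place is 0.4.

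The Background leads the reader to a standardised meaning. Its meta-analytic values are averages or ranges over several trials, some of which used different instruments, so they cannot be in units of one questionnaire. Someone who then meets an effect size of about 0.3 will place it among those values and conclude that the trial has 80% power for a standardised effect of 0.3.

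What is at stake is how the result is read. The first aim in the Discussion is to see whether earlier findings replicate in a psychiatric crisis population. If the primary comparison is not significant, the statement as worded would support the claim that an effect size of 0.3 was sought with 80% power and not found. That claim would overstate what the design can show.

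**Working it through.** **Inputs, all from Sample size calculation:** n = 90 per group; alpha = 0.05, one-sided; means 1.0 (EXP) and 1.3 (TAU); SD 0.80.

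**Step 1. Standardised effect.** d = (1.3 − 1.0) / 0.80 = 0.30 / 0.80 = 0.375.

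**Step 2. Reproduce the stated power.** For an unadjusted two-sample t test, the degrees of freedom are 2 × 90 − 2 = 178 and the noncentrality is d × √(n/2) = 0.375 × √45 = 0.375 × 6.708 = 2.52. Power is the probability that a noncentral t variable with these parameters exceeds the one-sided 5% critical value of 1.65. This gives 80.5% (normal approximation 80.8%). The number needed for 80% is 89 per group (88 by the normal approximation), against 90 planned. The plan's figure is reproduced. A two-sided 5% test would give about 71% and does not reproduce it, so the calculation was one-sided, as stated.

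**Step 3. Power if 0.3 is standardised.** With SD 0.80, d = 0.30 corresponds to 0.30 × 0.80 = 0.24 GSI points. Noncentrality = 0.30 × 6.708 = 2.01; power = 64.1% (normal approximation 64.3%). The chance of missing such an effect is 100 − 64 = 36%. For scale only, 80% power at d = 0.30 would take 139 per group (138 by the normal approximation).

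**Step 4. Smallest standardised effect with 80% power at 90 per group.** Normal approximation: (1.645 + 0.842) × √(2/90) = 0.371, which is 0.371 × 0.80 = 0.297 GSI points. This again shows that the 0.3 in the text is in GSI points.

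**Step 5. The cited range.** The article does not name the metric of the .23 to .33 range. If those values are standardised mean differences (an assumption), the power with 90 per group is:

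| Standardised effect | Noncentrality | Power, one-sided 5% |
|---|---|---|
| 0.23 | 1.54 | 46% |
| 0.30 | 2.01 | 64% |
| 0.33 | 2.21 | 71% |
| 0.375 | 2.52 | 80.5% |

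**Step 6. Effect of baseline adjustment.** If the analysis adjusts for baseline and the correlation between baseline and week 12 is r, the residual SD shrinks by √(1 − r²). The article gives no r, so these values are assumptions. With r = 0.5, power is about 75% at d = 0.30 and about 89% at d = 0.375. To reach about 80% at d = 0.30, r must be about 0.6.

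**The case against.** The strongest reply is that nothing has been miscalculated. The sentence gives the group size, alpha, sidedness, both means, the SD and the time point, and together they yield 80% power. A reader can recover 0.375 at once, and calling a raw mean difference an effect size is loose but not unheard of. On that reading the chance of missing the planned difference is about 20%. This stands: the defect is one of labelling, and the figure of 64% applies only when effect size is taken as standardised.

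The 64% also comes from a simple two-sample test, while the primary analysis is a repeated-measures comparison against baseline that may be more precise. This stands too, so the figure should be called unadjusted. The power statement itself claims no such gain and gives no correlation.

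A reader might go further in three ways that the document does not support:
- **That the sample size is wrong.** It is right for its own means and SD.
- **That the trial cannot detect effects of the size seen before.** The metric of the .23 to .33 range is not stated, and the Background also cites an average of 0.39, above the planned 0.375. Even on the standardised reading, 71% power at 0.33 is reduced power and not an inability to detect.
- **That losses before week 12 make the 80% unattainable.** "An estimated total of 180 patients, aged 18 years and over, will be included in the study", which equals 2 × 90. An allowance for loss is commonly left to the full protocol, and any missingness rate would be the reviewer's assumption. No finding is made on this.

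**Conclusion.** The point holds as an error of labelling in a planning figure. The effect that has 80% power is 0.30 GSI points, a standardised effect of 0.375, and not a standardised effect of 0.3. In the sense that the Background gives the term, the statement overstates unadjusted power by about 16 percentage points (80% against 64%).

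The values 0.375, 80.5% and 64% rest only on the article's own inputs and an unadjusted one-sided two-sample t test. The range of 46% to 71% also assumes that the cited .23 to .33 values are standardised mean differences. Baseline adjustment could raise all of these powers, by an amount that the article does not let one calculate.

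This is a modest correction. Group size, test and endpoint are unaffected.

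**What to change.** Replace the wording by: with 90 patients per group and a one-tailed alpha of 0.05, a difference of 0.30 GSI points at 12 weeks (means 1.0 and 1.3, SD 0.80; standardised effect 0.375) can be detected with 80% power.

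Add one sentence saying that unadjusted power at a standardised effect of 0.30 is about 64%, so that a null result is not read as well-powered evidence against an effect of that size. If the authors want to relate the design to the .23 to .33 range, they should first confirm its metric. If it is a standardised mean difference, they can give power of about 46% to 71% before any gain from baseline adjustment.

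The cost is a rewrite of one short paragraph and a less favourable stated detectable effect. The sample size stays as it is.
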